### Progression criteria and rationale

Progression criteria have been outlined to determine whether it is appropriate to progress to a subsequent adequately powered RCT, shown in table 2. Findings from the primary and secondary quantitative outcomes will be incorporated with the qualitative findings to inform decisions regarding an ‘intermediate’ results in any domain (ie, upgrade to feasible or downgrade to non-feasible). All recommendations will be reviewed by the trial steering committee (TSC). For criteria judged to be intermediate or non-feasible, the study team will examine the likely causes and consider whether a mitigation strategy could be successfully implemented.

**Table 2 T2:** Progression criteria for the JAKPPPOT trial

Domain	Non-feasible	Intermediate	Feasible
Recruitment: proportion of potential participants identified who enrolled in the trial	<20%	20–40%	>40%
Adherence: proportion of participants achieving ‘Good’ adherence (>80% of medication taken as prescribed)	<20%	20–80%	>80%
Acceptability: proportion of participants who view JAK inhibitor therapy in PPP to be ‘acceptable’	<20%	20–80%	>80%

JAK, Janus kinase; JAKPPPOT, Janus kinase inhibitors in palmoplantar pustulosis: a mixed-methods feasibility; PPP, palmoplantar pustulosis.

### Recruitment

A low recruitment rate is assumed, in line with the APRICOT study (17% overall recruitment rate).^16^ Factors in favour of a higher recruitment rate than the APRICOT are the single-arm trial design and the use of an oral tablet medication versus a daily subcutaneous injection with a high burden of injection site reactions. Factors negatively impacting recruitment are that this is a feasibility study rather than an efficacy study, there is no associated open-label extension and the potential side effect profile of upadacitinib. Optimisation strategies will be implemented through the trial to improve recruitment.

Secondary quantitative outcomes will be incorporated into the feasibility assessment, for example, failure to recruit 20 participants within 24 months would be an indicator of non-feasibility. If recruitment cannot be achieved in the context of an open-label trial, it is strong evidence against the feasibility of an adequately powered RCT.

### Adherence

Adherence will be assessed by counting any remaining medication via inspection of medication packaging at the end of each 4-week period (visit 3 and visit 4) to determine the proportion of days covered (total medication taken/total medication dispensed). If the packaging is unavailable, participants’ responses to the Voils DOSE-Nonadherence measure will be used as a surrogate.^27^

A high adherence rate is expected for several reasons. The tablet is easy to administer, and there is a relatively high burden of clinic visits over the 8-week treatment period. This will remind participants to take the medication and allow any compliance issues to be identified and addressed quickly.

Previous studies have demonstrated an association between an adherence rate of >80% and improved outcomes, when compared with an adherence rate of <80%, in certain disease contexts (eg, following a myocardial infarction).^28 29^ An 80% adherence threshold is often used, therefore, as a key measure of adherence in the context of clinical trials.^30^

The optimal threshold for adherence will differ depending on the specific disease, medication and population in question. Given the paucity of current literature regarding the use of upadacitinib in the management of PPP, it is not currently possible to determine the necessary adherence threshold for this specific context, and so the accepted threshold of >80% adherence rate has been used.^30^ Given the small numbers of trial participants, a wide intermediate progression criteria window has been specified, allowing findings from the integrated qualitative study to be incorporated into the analysis.

### Acceptability

The recent safety concerns regarding the use of this drug class among those at risk of cardiovascular disease may render them unacceptable to people with PPP, a population in which smoking is prevalent.^7 31^ However, there are several factors that may mitigate these concerns. There is a growing body of evidence to support the safety and efficacy of JAK inhibitors in the management of other medical conditions, with upadacitinib well-tolerated in the context of atopic dermatitis.^32^ The ease of administration is also a factor cited by patients in support of their acceptability.^33^ Given the lack of effective treatment options available for this condition, resulting in marked unmet clinical need, participants may be more willing to consider treatment with a JAK inhibitor in spite of side effect concerns.^3^ Finally, MHRA guidance has been incorporated into the study design, ensuring those most at risk from JAK inhibitor treatment are not eligible to take part. Given the small number of trial participants, a wide intermediate progression criteria window has been specified, allowing findings from the integrated qualitative study to be incorporated into the analysis.

### Participant recruitment

Potentially eligible trial participants will be identified via a number of means, including routine care visits, existing participants of related research studies who have consented to recall and self-referral following advertisement through national (eg, Psoriasis Association) and regional communication channels (newsletters, websites and social media). Participants can choose to participate in the trial and/or the semistructured interviews. Written, informed consent will be obtained by a physician (online supplemental file 2).

### Study procedures

The full study activities at each visit are outlined in table 3. The patient participant pathway consists of three periods: a screening period, a treatment period and a follow-up period. The screening period is up to a maximum of 3 months. Patients who fail the screening process may be re-screened if clinically appropriate.

**Table 3 T3:** Schedule of trial activities

	Screening (<3 months between screening and baseline)	Treatment period				Follow-up	Safety follow-up
**Allowed visit window:** **+** **3 days**	**Visit 0**	**Visit 1**	**Visit 2**	**Visit 3**	**Visit 4**	**Visit 5**	**Visit 6**
		Baseline	(week 1)	(week 4)	(week 8)	(week 12)	(week 20)
	Study enrolment	Treatment initiation			Treatment end	Study end	
Written informed consent	X						
Inclusion/exclusion eligibility check and sign-off	X	X					
Demographics	X						
Medical history	X	X					
Social history	X						
Family history	X						
PPP history	X						
Clinical phenotyping of disease/concomitant psoriasis	X						
Physical examination	X						
Vital signs*	X	X	X	X	X	X	
PPPASI† (×2: blinded and unblinded assessment)	X	X	X	X	X	X	
Fresh pustule count†	X	X	X	X	X	X	
Total pustule count†	X	X	X	X	X	X	
PPP-IGA† (×2: blinded and unblinded assessment)	X	X	X	X	X	X	
PASI (plaque psoriasis only)	X	X	X	X	X	X	
BSA	X	X	X	X	X	X	
Patient global assessment	X	X	X	X	X	X	
DLQI		X			X	X	
EQ5D-5L		X			X	X	
DOSE-Nonadherence questionnaire			X	X	X		
Photography (palms and soles)		X	X	X	X	X	
CXR‡	X						
T-Spot.TB§	X						
HIV, HBV and HCV	X						
Safety bloods¶**	X^††^	X^††^	X	X	X	X	
bHCG (blood)‡‡	X	X			X	X	
Prescribing and dispensing trial IMP		X		X			
Retrieval of IMP packaging (pill count)				X	X		
Acceptability Questionnaire§§		X				X	
RCT scoping question						X	
Concomitant meds	X	X	X	X	X	X	X
Adverse events monitoring		X	X	X	X	X	X
**Integrated qualitative study**							
Trial participant interview	X				X		
Trial decliner interview	X						
Healthcare professional interview	Interviews will take place with healthcare professionals throughout the duration of the trial (maximum one interview per healthcare professional)						

* Vital signs include heart rate, blood pressure, oxygen saturations, respiratory rate and temperature.

† Assessed by independent blinded assessor. PPPASI and PPP-IGA were also assessed by a second assessor.

‡ CXR not indicated if participant has had a CXR in the previous 12 months for clinical purposes.

§ T-Spot.TB not indicated for those participants known to have been successfully treated for TB (completed the prescribed treatment courses) as screening test is not clinically indicated. If unsure, please seek specialist advice.

¶ Safety bloods comprise WBC, Hb, platelet count, creatinine, urea, sodium, potassium, bilirubin, aspartate aminotransferase, alanine transaminase, HbA1c and cholesterol.

** CRP to be collected at baseline (visit 1) only.

†† If the time between screening and baseline safety assessment bloods is >4 weeks (ie, for participants washing out for 3 months from biologic therapy) the participant should be asked to attend for additional safety assessment blood tests. If feasible, this should be on the same day as the baseline visit allowing for time to clinically review the results before the first treatment dose (in which case only one set of baseline safety assessment bloods should be taken); however, if not convenient, it should be scheduled within 4 weeks of the baseline visit (these may be taken by their GP). If the participant attends an extra visit for these tests, then they should also go on to complete the full baseline visit, that is, repeat the baseline safety assessment bloods as scheduled.

‡‡ bHCG not indicated or applicable for postmenopausal women.

§§ Acceptability questionnaires will be completed during Visits 1 and 5 for participants not taking part in the integrated qualitative study (qualitative study participants will complete the questionnaires during the interviews).

bHCG, beta-human chorionic gonadotropin; BSA, body surface area; CXR, chest X ray; DLQI, Dermatology Life Quality Index; EQ5D-5L, European Quality of Life 5 Dimensions 5 Level Version; Hb, haemoglobin; HBV, Hepatitis B virus; HCV, Hepatitis C virus; IMP, investigational medical product; PPP, palmoplantar pustulosis; PP-PASI, Palmoplantar Pustulosis Psoriasis Area and Severity Index; PPP-IGA, Palmoplantar Pustulosis-Investigator Global Assessment; RCT, randomised controlled trial; TB, tuberculosis.

The treatment period (visits 1–4) is 8 weeks. At the start of the treatment period, eligible patient participants will receive upadacitinib, to be administered daily as an oral tablet for 8 weeks. Participants will receive 4 weeks of medication at Visit 1 (baseline) and Visit 3 (week 4).

The follow-up period (visit 5) at week 12 will be used to assess disease relapse off study treatment, follow-up any adverse events and plan for post-trial management of their condition. Participants will also be asked the following question to scope out their views on a future RCT: ‘Would you be interested in participating in a trial similar to this with either a dummy arm or active comparison drug arm in the future?’. A final safety review (visit 6) will be carried out at week 20 to assess for any further adverse events.

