Adults (18 years and over) with a diagnosis of palmoplantar pustulosis* made by a trained dermatologist with disease of sufficient impact and severity to require systemic therapy Disease duration of ≥6 months, not responding to an adequate trial of topical therapy including very potent corticosteroids Evidence of active pustulation on palms and/or soles At least moderate disease based on a Palmoplantar Pustulosis Investigator Global Assessment Able to give written, informed consent to participate Willing and able to comply with scheduled visits, treatment plan, laboratory tests and other study procedures.	A history of malignancy of any organ system (other than treated, localised non-melanoma skin cancer), treated or untreated, within the past 5 years A history of provoked or unprovoked venous thromboembolism (deep vein thrombosis or pulmonary embolism), unless actively treated with long-term anticoagulation Previous systemic treatment with a JAK inhibitor A history of recurrent bacterial, fungal or viral infections which, in the opinion of the principal investigator, present a risk to the patient Evidence of active infection or untreated latent tuberculosis HIV positive Active or untreated Hepatitis B or C Use of therapies with potential or known efficacy in psoriasis during or within the specified timeframe before treatment initiation as listed in the washout section Moderate renal impairment (CrCl < 50 mL/min) Neutropenia (<1.5×10^9^/L) Thrombocytopenia (<150×10^9^/L) Moderate hepatic disease and/or raised hepatic transaminases (ALT/AST) > 2 x upper limit of normal at baseline. Patients who fail this screening criterion may still be considered following review by a hepatologist and confirmed expert opinion that study entry is clinically appropriate. Live vaccinations within 3 months prior to the start of study medication, and no planned live vaccinations during the trial and up to 3 months following last dose Women who are pregnant, breast feeding or of childbearing potential not on adequate contraception Male participants who are not willing to use highly effective methods of contraception when engaging in sexual activity with a female of childbearing potential Any condition where, in the opinion of the investigator, the investigational medical product would present risk to the patient. Unable to give written, informed consent. Unable to comply with the study visit schedule Known hypersensitivity to upadacitinib and/or its excipients (SmPC 6.1) Receipt of any of the following within the specified timeframe before treatment initiation (baseline, visit 1): Topical treatments likely to impact signs and symptoms of psoriasis (eg, potent/very potent corticosteroids, vitamin D analogues, calcineurin inhibitors) within 2 weeks Systemic immunosuppressants (eg, methotrexate, ciclosporin, acitretin) within 4 weeks Phototherapy (UVB TL01, UVB, PUVA, UVA1) within 4 weeks Etanercept or adalimumab within 4 weeks Other biologic therapies (infliximab, certolizumab, ustekinumab, secukinumab, ixekizumab, risankizumab, bimekizumab, brodalumab, tildrakizumab, guselkumab) within 3 months Other investigational drugs within 4 months or five half-lives (whichever is longer) Other immunosuppressant/immunomodulatory therapies including intra-articular steroids within 30 days or five half lives (whichever is longer)

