### Concomitant medication

Emollient therapy and mild-moderate topical corticosteroids will be permitted throughout the trial. Investigator-directed use of potent/super potent topical corticosteroids as ‘rescue’ therapy can be used if necessary, with the volume used recorded at study visits to evaluate any potential confounding effect.

Systemic therapies that are likely to have efficacy in PPP or to compound the immunosuppressive effects of upadacitinib are prohibited. If treatment with these is essential, the participant must notify the study team and they will be withdrawn from the trial.

Guidance from the clinical trials facilitation and co-ordination group will be followed regarding effective forms of contraception during the trial.

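### No pregnancy test is scheduled at Visit 3 (week 4), when blood is drawn and the second 4-week supply is dispensed, so a pregnancy detectable then waits until week 8 for a scheduled test

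*Protocol article*

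**What the plan says.** Table 1 (Study population) excludes "Women who are pregnant, breast feeding or of childbearing potential not on adequate contraception". For the treatment period, the Concomitant medication section adds: "Guidance from the clinical trials facilitation and co-ordination group will be followed regarding effective forms of contraception during the trial".

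Table 3 (Study procedures) has three rows that bear on this point:

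- **bHCG (blood):** marked at Visits 0, 1, 4 and 5; blank at Visits 2 and 3. A footnote exempts postmenopausal women.
- **Safety bloods:** marked at Visits 0 to 5, so blood is drawn at Visit 3.
- **Prescribing and dispensing:** marked at Visits 1 and 3. The text agrees: "Participants will receive 4 weeks of medication at Visit 1 (baseline) and Visit 3 (week 4").

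The footnote on safety bloods itemises the panel: "Safety bloods comprise WBC, Hb, platelet count, creatinine, urea, sodium, potassium, bilirubin, aspartate aminotransferase, alanine transaminase, HbA1c and cholesterol". The one stated variation is CRP: "CRP to be collected at baseline (visit 1) only". Pregnancy testing therefore takes place only where the bHCG row is marked.

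Table 1 also sets a neutrophil limit of 1.5×10^9/L and a platelet limit of 150×10^9/L. The panel names the platelet count, but gives white cells only as WBC.

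**The concern.** The protocol treats pregnancy as a reason not to give the drug and checks for it twice before the first dose. Visit 3 is the second point at which the trial team hands over drug, and the only one during treatment. Blood is taken at that visit, yet the pregnancy check made before the first dispensing is not repeated before the second. A participant who conceived after baseline, and in whom this was already detectable at week 4, could be given the second supply and finish the course before the next scheduled test.

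What is at stake is the safety of a participant and a possible fetus. The primary feasibility outcomes, the PP-PASI comparison with the historic controls and the progression criteria are not affected.

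**Working it through.** The protocol states no figure for this point. The check sets the bHCG and dispensing rows of Table 3 side by side and counts days.

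**Inputs**

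- bHCG tests at screening and weeks 0, 8 and 12 (Table 3).
- Drug dispensed at weeks 0 and 4, 4 weeks each time (Table 3; Study procedures).
- One tablet daily for 8 weeks (Intervention).
- Visit window of 3 days either side (Data collection and management).

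**Doses**

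Whole course: 8 × 7 = 56 daily doses. Each supply: 4 × 7 = 28 doses. The second supply is 28/56, half of the course. The option of 15 mg in place of 30 mg does not change the count.

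**Interval between scheduled tests on treatment**

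- As planned: week 8 − week 0 = 8 weeks = 56 days.
- With a test at Visit 3: 4 weeks + 4 weeks, so the longest interval is 28 days.

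**Who would be found earlier**

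| Pregnancy first detectable | Found as planned | Found with Visit 3 test | Gain |
|---|---|---|---|
| By baseline | Visit 0 or 1 | Visit 0 or 1 | none |
| After baseline, by week 4 | week 8 | week 4 | 4 weeks |
| After week 4, by week 8 | week 8 | week 8 | none |
| After week 8, by week 12 | week 12 | week 12 | none |

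Only the second row gains. The nominal gain is 56 − 28 = 28 days. If both visits may move by 3 days, it is 28 ± 6, or 22 to 34 days. The doses that could be avoided are capped by the second supply: at most 28.

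**How many women**

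The protocol does not say how many participants will be of childbearing potential. If the sex mix follows APRICOT (84% female; Equality, diversity and inclusion), then 20 × 0.84 = 16.8, or about 17 women. The background says that PPP typically presents in middle age, so the number who need the test may be well below that. The extra assays cannot exceed 20, the planned enrolment.

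**The white-cell wording**

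Neutrophil count = WBC × neutrophil share. At an assumed WBC of 3.0×10^9/L, a 40% share gives 3.0 × 0.40 = 1.2 (excluded) and a 60% share gives 3.0 × 0.60 = 1.8 (eligible). If the share is assumed to lie between 30% and 70%, the limit of 1.5 falls at a WBC between 1.5/0.70 = 2.1 and 1.5/0.30 = 5.0. Within that band a total count alone does not settle the criterion; outside it, under the same assumption, it does. This is a reason to make the wording explicit. It does not show what will be measured.

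**The case against.** The strongest reply is that the schedule breaks no rule. Women of childbearing potential must use adequate contraception to enter, recognised guidance on contraception applies during the trial, two tests precede dosing, and tests follow at weeks 8 and 12. Treatment lasts only 8 weeks. The protocol sets no 4-weekly testing interval, and the 28 doses are a worst case that needs contraception to fail early enough to be detectable at week 4. All of this stands. It limits the point to an inexpensive gain in detection time. It does not remove the gain, because the sample is already being taken when the drug is handed over.

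A reader might go further on either of two lines, and the document supports neither.

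- **That pregnancies would be missed.** They would not be missed by the schedule: any pregnancy detectable at week 4 that continues meets a scheduled test at week 8.
- **That the neutrophil exclusion ("Neutropenia (<1.5×10^9^/L") cannot be verified because the panel lists only WBC.** In a footnote to a condensed article, WBC may well stand for a count with differential, and the full protocol is not shown. The criterion has a numerical limit, and eligibility is signed off at Visits 0 and 1, so the plan already requires the neutrophil value. Creatinine clearance is not in the list either; it has to be derived from creatinine. The provision that extra pre-baseline bloods may be taken by a GP does not change this, because a participant who attends an extra visit for them must still have the baseline bloods repeated.

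**Conclusion.** The point holds as a minor, low-cost safety improvement, not as an error. Table 3 leaves 8 weeks between scheduled pregnancy tests on treatment and omits the test at the one on-treatment visit where drug is dispensed. In an affected participant, a Visit 3 test would bring detection forward by 4 weeks (22 to 34 days with the visit windows) and could avoid up to 28 of 56 doses. This assumes that the pregnancy is detectable at week 4, that it would not otherwise have come to light, and that the result is acted on before the second supply is started. The chance of such a case cannot be estimated from the document and may be small. Nothing in the analysis changes.

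The white-cell wording is an editorial clarification only.

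**What to change.** In Table 3, mark bHCG at Visit 3, taken from the safety-blood sample, for women to whom the test applies. Add a footnote that the result is to be reviewed before the first tablet of the second supply is taken, either by a same-day result or by dispensing with telephone release.

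The cost is one extra assay per woman tested, with no extra visit or venepuncture. The real burden is turnaround: a delayed result could interrupt daily dosing at week 4. The release procedure should therefore be settled in advance, and any pause that it causes should be recorded so that it is not read as poor adherence.

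While the footnotes are open, change WBC to WBC with differential in the list of safety bloods, so that it matches the neutrophil exclusion. If the full protocol already says this, only the published wording needs to change.

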### Study design

JAKPPPOT is an open-label, single-arm, mixed-methods feasibility trial, conducted at St John’s Institute of Dermatology, Guy’s and St Thomas’ NHS Foundation Trust, UK (figure 1). Participants (n=20) will receive 8 weeks of treatment with the JAK inhibitor upadacitinib (‘Rinvoq’, 30 mg, once-a-day). Integrated qualitative semistructured interviews (up to n=40) will be undertaken with trial participants, trial decliners and healthcare professionals. Recruitment optimisation strategies will be identified and implemented via the QRI process incorporated into this trial. The study endpoint is 20 participants successfully recruited, or 24 months elapsing, whichever occurs first.

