### Outcomes

#### Primary outcomes

The following outcomes will be assessed after 24 months of recruitment, or when the recruitment target of 20 participants is achieved (whichever occurs first):

Overall proportion of potential participants identified who enrolled in the trial, termed the ‘recruitment rate’.‘Potential participants identified’ is defined as those who have direct contact with the research team.Overall proportion of participants achieving ‘good adherence’ (proportion of days covered >80%) during the trial.‘Proportion of days covered’ is defined as the total medication taken during the 8-week trial period as a proportion of the total medication dispensed.Overall proportion of participants who view JAK inhibitor therapy in PPP to be ‘acceptable’.Acceptability will be measured based on responses to the following question at the end of the 8-week treatment period: ‘Overall, how acceptable was taking upadacitinib to you?’A 5-point Likert scale will be used, with answers dichotomised into acceptable (acceptable/completely acceptable) or unacceptable (completely unacceptable/unacceptable/neutral)

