### Integrated qualitative study

Qualitative research will be integrated into the trial to provide fundamental insights into the feasibility and design of a definitive trial. Qualitative interviews will be undertaken in the following three cohorts:

Trial participants: semistructured interviews before and after the 8-week treatment period (up to 20 interviews).Trial decliners: one semistructured interview per trial decliner (up to 10 interviews). Trial decliners are individuals who have been invited to participate in the clinical trial and then declined.Healthcare professionals: one semistructured interview per healthcare professional (up to 10 interviews).

Qualitative interviews will be undertaken by an appropriate, delegated member of the research team. These interviews will be conducted either in person or online via Microsoft Teams, depending on participant preference. Interview topic guides will be used to ensure similar areas are covered with each participant, but will be sufficiently flexible to encourage the interviewees to express their own views about the study. We will aim to interview up to 10 eligible participants in each cohort, or up until data saturation has been reached (no new themes were generated after three sequential participant interviews).

The semistructured interviews will be recorded, transcribed verbatim and thematically analysed.^35^ Transcripts will be reviewed and coded thematically using the NVivo 15 software package, identifying key insights, experiences or opinions. Coded interviews will be reviewed and compared so as to characterise recurrent and/or prioritised ideas about the study and interventions. The perspectives of different participants will be compared and synthesised in this process in order to reflect on similar and different experiences. Analytic codes and themes will be tested and refined as new data are considered. The results will be triangulated with the other study findings to inform recommendations for implementing trial findings and the design of the future definitive RCT. Differences in prospective and retrospective acceptability will be explored via comparison between the pretrial and post-trial interview responses.^36^

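### The primary acceptability item is answered by up to half the participants during a recorded interview at week 8 and by the rest at a week 12 visit, so setting and timing are confounded in one 20-person proportion

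*Protocol article*

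**What the plan says.** The Primary outcomes section fixes both the item and its timing: "Acceptability will be measured based on responses to the following question at the end of the 8-week treatment period". The item reads "Overall, how acceptable was taking upadacitinib to you". It has five response levels, with "answers dichotomised into acceptable (acceptable/completely acceptable) or unacceptable (completely unacceptable/unacceptable/neutral" on the negative side, so a neutral reply counts against acceptability.

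Table 2 (Progression criteria and rationale) grades "Acceptability: proportion of participants who view JAK inhibitor therapy in PPP to be ‘acceptable" as feasible above 80%, intermediate from 20% to 80% and non-feasible below 20%.

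The Table 3 footnote then sets two routes for collecting the answer. For one group, "Acceptability questionnaires will be completed during Visits 1 and 5 for participants not taking part in the integrated qualitative study"; Visit 5 is week 12. For the other group, "qualitative study participants will complete the questionnaires during the interviews". The participant-interview row of Table 3 is marked at screening and at Visit 4 (week 8).

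The Integrated qualitative study section adds that "Qualitative interviews will be undertaken by an appropriate, delegated member of the research team", in person or online, and that interviews are recorded. It aims for at most 10 people per cohort, or fewer if saturation comes first. The Participant recruitment section lets people choose whether to take part in the trial, the interviews or both.

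**The concern.** The two groups differ in two respects at once. One answers within a recorded conversation about the study and the treatment, at the end of the treatment course. The other answers at a visit four weeks after the last scheduled dose, and the Study procedures section uses that visit to look at relapse off treatment. Either difference could alter the reply to a single overall rating. Only the first time point agrees with the definition under Primary outcomes.

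The mix is not fixed in advance. It depends on who agrees to be interviewed and on when saturation is declared, so route is also tied to self-selection. The pooled proportion feeds a three-band decision on progression to a definitive trial, and at 20 participants one reply can change the band. There is a further cost. Qualitative findings are meant to help settle intermediate results, but for interviewees the score would be produced inside the source that is later used to interpret it.

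**Working it through.** **Inputs from the article.** Target of 20 participants (Study design: "The study endpoint is 20 participants successfully recruited, or 24 months elapsing, whichever occurs first"); at most 10 interviewed participants (Integrated qualitative study, consistent with up to 20 interviews held before and after treatment); feasible above 80% (Table 2).

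**Inputs assumed.** True acceptability of 70%, 75% or 80%, and a shift of 5 to 15 percentage points in the interviewed group, in either direction. The article gives neither figure.

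**The plan's own figure.** No precision is stated for acceptability. The only 20-person proportion quantified is adherence: 75% with a 95% CI of 51% to 91%. The exact (Clopper-Pearson) interval for 15/20 is 50.9% to 91.3%, which reproduces it.

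**Share interviewed.** 10/20 = 50% at full recruitment. If recruitment stopped at 15, it would be 10/15 = 67%.

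**The cut.** 16/20 = 80.0% is not above 80%, so it is intermediate (exact 95% CI 56% to 94%). 17/20 = 85% is feasible (62% to 97%). One reply moved between neutral and acceptable changes the band.

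**One route for all 20.** X ~ Bin(20, p). At p = 0.75, P(X ≥ 17) = 0.1339 + 0.0669 + 0.0211 + 0.0032 = 0.225.

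**Two routes, 10 and 10.** A ~ Bin(10, p) for visit answers, B ~ Bin(10, p + d) for interview answers, and P(A + B ≥ 17) = Σ P(A = k) · P(B ≥ 17 − k) for k = 7 to 10. With p = 0.75 and d = +0.10:

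- k = 7: 0.2503 × 0.1969 = 0.0493
- k = 8: 0.2816 × 0.5443 = 0.1533
- k = 9: 0.1877 × 0.8202 = 0.1540
- k = 10: 0.0563 × 0.9500 = 0.0535
- Sum = 0.410

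P(at least 17/20) for other values, with p the rate among the 10 visit answers:

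| p | d = −0.10 | d = −0.05 | d = 0 | d = +0.05 | d = +0.10 | d = +0.15 |
|---|---|---|---|---|---|---|
| 0.70 | 0.043 | 0.070 | 0.107 | 0.158 | 0.223 | 0.306 |
| 0.75 | 0.106 | 0.158 | 0.225 | 0.309 | 0.410 | 0.525 |
| 0.80 | 0.223 | 0.309 | 0.411 | 0.526 | 0.648 | 0.769 |

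**Could the analysis detect a difference between routes?** Take 10 v 10 at 75% v 95%, two-sided 5%, normal approximation. The null SE is √(2 × 0.85 × 0.15 / 10) = 0.160 and the alternative SE is √((0.75 × 0.25 + 0.95 × 0.05) / 10) = 0.153. Power = Φ((0.20 − 1.96 × 0.160) / 0.153) ≈ 0.23. A 20-point difference would usually be missed. If one were found, it could not be attributed to setting, timing or self-selection.

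**The case against.** A reader might infer that interviewer pressure will push the result above 80%. The article does not support that. It uses the same verb, complete, for both groups, which fits a form the participant fills in; it does not say that the interviewer reads the item aloud or sees the reply. It does not show that visit answers are more private, and Visit 5 is also where staff plan further care. An interview designed to draw out a participant's own views could bring out reservations and lower the rating. The size of any shift has no source, and 10 interviewees is a ceiling. All of this stands, and for that reason the direction is left open here and the calculations are labelled illustrative.

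It can also be said that 17/20 is not a rigid gate. An intermediate 16/20 may be upgraded on qualitative findings, the steering committee reviews all recommendations, acceptability is one of three domains, no hypothesis is tested, and the confidence interval will show the uncertainty. This also stands and limits the consequence. It does not remove the problem, because the committee would be reading the mixed number.

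Finally, form administration is a detail that an article may leave to the full protocol. That is fair for who hands out the form and whether it is private. It does not cover the two routes themselves, which the footnote states as a rule, or the week 12 time point, which does not match the article's own outcome definition.

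**Conclusion.** The concern holds as a defect in how a primary outcome is collected. One single-item proportion mixes two settings and two time points; up to half of 20 participants are in the interview group, and more if fewer enrol; and the week 12 route disagrees with the Primary outcomes section. Setting and timing are confounded with each other and with the choice to be interviewed, and the sample is too small to separate them afterwards.

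The size of the effect on the grade is unknown. If the true rate were 75% and 10 interviewees shifted by 10 points, the chance of a feasible grade would move from 0.23 to 0.41 upward or 0.11 downward. Those figures rest on assumed rates, an assumed shift, the maximum number of interviewees and independent answers. They show how sensitive the cut is. They do not show that the grade will be inflated, and nothing in the article establishes that interviews raise ratings.

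**What to change.** Change the acceptability row and footnote of Table 3 so that every participant, interviewed or not, self-completes the existing form at one common time point that matches the Primary outcomes section: Visit 4, at the end of the eight weeks of treatment. For interviewees this should happen before the post-treatment interview starts. State that only this answer counts towards the primary outcome, and let the interview explore the reasons for it afterwards. Both parts are needed: aligning the visit alone would leave up to half the answers inside the interview, and moving the form ahead of the interview alone would leave the week 8 v week 12 split.

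The cost is a minor change to the form schedule. Visit 4 is already an attended visit, the form exists, and no extra visits or staff are required.
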